##### Children’s Perspectives

As evident in the PRO-ECO values seen in Figure 1, the Steering Committee centers the child and their wellbeing, surrounded by the caregivers and community that support them. Steering Committee members emphasized the importance of hearing directly from children about their perspectives. They also stressed the importance of strength-based measures, rather than deficit-based measures. This was in contrast to our approach in the PRO-ECO 1.0 study, where we had relied on questionnaires completed by ECE staff about the children, which examined difficulties, such as conduct problems, aggression, and depressed affect.

For this study, we adapted the Early Childhood Education and Care Well-being Monitor, a structured interview designed for ECE staff to gather the input of children aged 4 to 6 years regarding their well-being in the ELCC center [47,48]. It includes questions about the children’s daily experiences at the center (eg, “Do you think it’s fun here?”), their activities (eg, “Tell me about some of your favorite things to do here.”), relationships with other children (“eg, Do you have some good friends here?”) and the ECEs (eg, “Do you want adults to play with you more?”), the physical environment (eg, “What is your favorite place outdoors here?”), and the extent to which their views are listened to (eg, “Do the adults decide what you are going to do when you are outdoors here?”). For this study, we eliminated questions related to the indoor physical environment and adapted the remaining questions to suit our study’s context, for a total of 23-25 questions, depending on the time point (pre- or postprogram). These questions guided semistructured interviews with each child, and we referred to the mosaic approach for listening to young children to further facilitate children’s participation [49]. For example, children were shown images of 3 faces, a green smiley face, a yellow neutral face, and a blue frowny face, which they could point to for each question to support their responses.

Child interviews were conducted for each individual child on-site by the ECEs at the participating ELCC center. Due to the time and resources required to conduct interviews with children, we collected these data at time 1 (preprogram) and time 3 (postprogram) only. ECEs identified a child from the consented study participant list and found a quiet place, preferably outside, to conduct the interview. Using a video camera, ECEs introduced the interview activity to the child and gained the child’s assent to ask them questions. A child could remove assent at any point by declining to continue. Following the interview, ECEs noted down notable features of the interview, such as: if the child moved around or was distracted; if other children joined in the interview; if the child made body language movements that the audio would not capture; or to reflect on impressions and note down some immediate thoughts. For children who required additional support or nonverbal cues, emotion icons and images of different features in the child’s ELCC center’s outdoor space were provided. In addition, some ECEs found that walking around the outdoor space with the child during the interview could facilitate responses. ECE’s conducting interviews were trained to stop the interview if the child removed assent and not to force an interview if a child did not wish to participate.

##### ELCC Center Staff Perspectives

To gather staff perspectives on the PRO-ECO program, we conducted listening circles with each ELCC center at baseline (time 1) and after the center implemented the PRO-ECO program (time 2 for group 1 and time 3 for group 2). At baseline, questions that guided the listening circles included their perceptions of outdoor play and the outdoor space in their ELCC center, the current practice and pedagogy of outdoor play, their role in supporting outdoor play, and recommendations for implementing the PRO-ECO program. At the postimplementation listening circle, we queried the changes they noticed, what they liked and did not like, how the program changed their practice, and any notable observations relevant to the effect of PRO-ECO on the children and family engagement. The listening circles were conducted in ways that best fit the ELCC center needs, such as scheduling them during already existing staff meetings. Staff time was covered by the funding provided to each center.

##### Family Perspectives

To gather family perspectives on outdoor play changes they may have noticed after the implementation of the PRO-ECO program at their child’s center, we provided a brief survey and conducted short one-on-one interviews in-person and over Zoom. We sought their reflections on any changes they may have noticed in their children, the ECEs’ approach to outdoor play, and the outdoor space. Each survey participant was offered a CAD $10 (US $7) gift card, and interview participants received a CAD $50 (US $37) honorarium.

### Study Covariates

We collected data on the following covariates that have been found to influence children’s outdoor play: children’s demographics, including sex, age, disability status, first language spoken at home, family composition, average household income, and highest level of education completed by a household member. We collected information related to the child’s length of time at the ELCC center and their experiences with any other forms of formal care. This information was gathered through questionnaires completed by families at the time of the child’s enrollment in the study.

Weather conditions (eg, sunny, cloudy, heavy rain, snow) were recorded by the liaisons at the beginning and end of their play video recording sessions. Temperature data were recorded by the research team using weather network databases for the weather station closest to the ELCC center.

The following information related to recruitment, retention, and attendance was collected throughout the study:

Number of eligible children that were approached to participate in the study.Number of children who consented to participate, did not consent to participate, and did not respond.Number of children who withdrew from the study.Number of children who enrolled in the ELCC center after initiation of the PRO-ECO program.Number of children who left the ELCC after initiation of the program.Individual and center-wide attendance rates.

### Data Analysis

We aimed to collect 512 fifteen-second video clips at each center for each time point, for a total of 5120 video clips per time point (total N=15,360). This power calculation was based on the statistically significant effect size we observed in the PRO-ECO 1.0 study related to the short-term impact of the program on improving play occurrence (time 1 vs time 2 for group 1 and time 2 vs time 3 for group 2) [23]. The key coefficient of interest is the intervention by group interaction term, which corresponds with a *R*^2^ increase of 0.00295 (ie, variance explained by the special effect), equaling to an effect size of 0.00308, when this interaction term is added to the multivariate regression model. We also expect to have 5 control variables (ie, intervention, group, weather conditions, temperature, and child gender) in the multivariate regression models, which altogether correspond with a residual variance of 0.958. This supports a power calculation of over 99% (0.997) to detect the program effect that we observed in the PRO-ECO 1.0 study. The power calculation was conducted using the G*Power software [50].

To analyze the effect of the PRO-ECO program within the PRO-ECO 2.0 study, we intend to evaluate the change in nature play behavior between pre- and postprogram. The proportion of nature play occurrences compared with nonnature play occurrences across ELCC centers at baseline will be summarized by treatment group using frequencies and percentages. This approach mirrors our analysis in the PRO-ECO 1.0 pilot study [22,23], which demonstrated the effectiveness and significance of measuring children’s outdoor play occurrences through a comparison of play and nonplay behaviors pre- and postprogram implementation. However, in contrast to the PRO-ECO 1.0 study, this study focuses on the occurrence of nature play as the primary outcome variable, and not play participation in general.

Baseline demographic and ELCC characteristics will be summarized by group using means and SDs, medians and IQRs for continuous variables, and frequencies and percentages for categorical characteristics. Bivariable relationships between children’s demographic characteristics and outdoor nature play occurrence, both overall and by group, will be explored to identify potential confounding factors at the individual level, considering randomization occurs at the cluster level. Mixed effects models will be used to assess differences in quantitative outcome measures between groups, as well as within-group comparisons of pre- and postprogram implementation measures.

We will analyze child interviews using qualitative content analysis methods to systematically identify patterns and themes that reflect children’s perspectives and experiences on outdoor play and well-being [51]. The method’s adaptability to diverse data types and research contexts, combined with its structured and systematic analytical process, makes it particularly viable for exploring the wide-ranging and expressive nature of children’s responses. For ECE and family listening circles and interviews, we will use thematic analysis, which involves identifying and analyzing key themes within the data [52]. We will follow a reflexive thematic analysis to facilitate insights regarding ECEs’ and families’ perspectives on various interconnected topics, such as the importance of outdoor play, power dynamics, cultural norms on outdoor play, and the acceptability of the PRO-ECO program.

In alignment with the PRO-ECO project values and the partner research agreements, we will work with participating ELCC centers and the Steering Committee to share ongoing results from this study. Steering Committee members and liaisons will be invited to join a working group to work with the Outside Play Lab team on guiding and interpreting the analyses. We will gather ongoing iterative input from the broader Steering Committee and ELCC center teams to help interpret the findings, guide subsequent analyses, and develop recommendations. This form of member checking will seek to ensure all analyses and results align with the desired outputs of our project partners and appropriately convey the findings.

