**Methods:**

This study considered a 5 R’s research approach from its inception, beginning with the formation of a Steering Committee and over a year of relationship building before formal study activities commenced. A key early focus was collaboratively identifying project values through an iterative process. Collectively, we worked to promote equity, disrupt power dynamics, and embed Indigenous data sovereignty principles into research agreements, marking a significant departure from traditional Western research processes. The PRO-ECO program and study protocol are implemented in partnership with 10 ELCC centers delivering licensed full-day, year-round care to children aged 2.5-6 years in rural and urban areas of British Columbia, Canada. The PRO-ECO program includes 4 components to address common barriers to outdoor play in ELCC settings. Primary outcome measures include the proportion and diversity of observed nature play behavior during dedicated outdoor times at ELCC centers as measured through observational behavior mapping. Secondary outcomes include changes in educator attitudes, quality of ELCC outdoor play space, and children’s perspectives of their experiences at ELCC centers. Outcome data are collected at baseline, and 6 months and 12 months post baseline. The community’s perspectives (educators, children, and families) on the project are assessed qualitatively to understand the acceptability of the PRO-ECO program. Mixed-effect models will test the effect of the PRO-ECO program on quantitative outcomes. Qualitative data will support the interpretation of quantitative findings and provide evidence on project acceptability.

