### Data Collection and Measures

#### Primary Outcomes

Led by the values they identified as guiding the study (Figure 1), the Steering Committee sought to emphasize children’s relationship with the land and care for the environment. Thus, study outcomes were prioritized to understand how the PRO-ECO project influenced children’s engagement with the land. As a result, the primary outcome chosen for the PRO-ECO 2.0 study was the occurrence of outdoor nature play behavior at ELCC centers. While the primary study outcome differs from the PRO-ECO 1.0 study, where the occurrence of play versus nonplay was assessed, children’s outdoor play behavior was still coded using the expanded version of the Tool for Observing Play Outdoors (TOPO) [42]. The TOPO is designed to measure 8 play types (physical play, exploratory play, imaginative play, play with rules, bio play, expressive play, restorative play, and digital play) and one nonplay type, along with corresponding subtypes. For this study, we coded nature play behavior through the TOPO bio play behavior type, which includes subtypes for play (observing; discussing; or interacting with plants, wildlife, or natural materials, as well as playing in a way that demonstrates care or stewardship of the environment or appreciation of nature). To further refine observed nature play behavior, children’s environmental interactions (loose parts, fixed parts, natural elements, manufactured elements) were also recorded and coded.

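### The stated power of 0.997 is for the pilot's effect on play versus nonplay; it is not power for the primary outcome, nature play

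*Protocol article*

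**What the plan says.** Data Analysis in the protocol article rests the power calculation on the statistically significant "effect size we observed in the PRO-ECO 1.0 study related to the short-term impact of the program on improving play occurrence". The input is an R² "increase of 0.00295 (ie, variance explained by the special effect), equaling to an effect size of 0.00308", with a residual variance of 0.958 once five control variables are in the model. The result is a power of 0.997, and the article describes it as power for the program effect seen in the pilot. Inclusion Criteria and Recruitment points to this calculation for the desired 10 centers.

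Primary Outcomes states that "the primary outcome chosen for the PRO-ECO 2.0 study was the occurrence of outdoor nature play behavior at ELCC centers", coded through the bio play type of the TOPO, one of eight play types in that tool. It adds that "primary study outcome differs from the PRO-ECO 1.0 study, where the occurrence of play versus nonplay was assessed". Data Analysis repeats the distinction: "this study focuses on the occurrence of nature play as the primary outcome variable, and not play participation in general". The abstract widens the primary outcome further: "Primary outcome measures include the proportion and diversity of observed nature play behavior during dedicated outdoor times at ELCC centers".

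The article gives no baseline proportion, expected difference or power for nature-play occurrence or for diversity.

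**The concern.** The article announces the change of primary outcome but does not carry it into the power calculation. An R² increase depends on the prevalence of the outcome, the size of the effect on it and the variance that the covariates explain. All three may differ between any play and one type of play. Because nature play is a subset of play, its prevalence cannot exceed that of play.

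The observation method changed as well. According to Primary Outcomes, the pilot was coded in situ at center level, whereas this trial codes staff-recorded video at child level.

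At stake is how the result is read. A reader who takes 0.997 as the trial's power would treat a null finding on nature play as strong evidence of no effect, and nothing in the document supports that. The same reader cannot learn what change in nature play the trial could detect.

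This point is separate from clustering. The input would belong to the wrong outcome even if all clips were independent.

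**Working it through.** **1. Reproducing the stated figure.** Inputs from Data Analysis: R² increase 0.00295, residual variance 0.958, five control variables plus the interaction (6 predictors), 5120 clips per time point, 15,360 in total. Alpha is not stated; 0.05 is assumed.

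- f² = 0.00295 / 0.958 = 0.00308, as printed.
- Power comes from the noncentral F distribution with noncentrality λ = f² × N.
- N=10,240 (two time points, 2 × 5120) with 5 tested predictors gives 0.9970, which matches. That this was the setup used is an inference.
- With 1 tested predictor, power is 0.978 at N=5120, 0.9999 at N=10,240 and above 0.9999 at N=15,360.

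The arithmetic is sound for the pilot's effect on play versus nonplay.

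**2. Turning the pilot effect into percentage points.** This needs a play prevalence, which the document does not give; 80% is assumed. In a balanced two-by-two design, an interaction of size d (a difference in differences) explains d²/16 of the outcome variance p(1−p). So:

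- d = √(0.00295 × 16 × 0.80 × 0.20) = √0.00755 = 0.0869, or about 8.7 points.
- Relative to 80%, that is 0.0869 / 0.80 = 10.9%.

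**3. Carrying it to nature play.** Nature-play prevalences of 10% and 20% are assumed. For each, f² = d² / [16 × p(1−p) × 0.958]. The residual variance of 0.958 is kept for want of another value. The calculation uses 1 tested predictor, alpha 0.05 and clips treated as independent.

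| Assumed gain on nature play | Prevalence | d (points) | f² | Power, N=10,240 | Power, N=15,360 |
|---|---|---|---|---|---|
| Same relative gain (10.9%) | 10% | 1.1 | 0.000086 | 0.155 | 0.21 |
| Same relative gain (10.9%) | 20% | 2.2 | 0.00019 | 0.29 | 0.40 |
| Half the absolute gain | 10% | 4.35 | 0.00137 | 0.96 | >0.99 |
| Half the absolute gain | 20% | 4.35 | 0.00077 | 0.80 | 0.93 |
| Same absolute gain | 10% | 8.7 | 0.0055 | about 1.0 | about 1.0 |
| Same absolute gain | 20% | 8.7 | 0.0031 | about 1.0 | about 1.0 |

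Example, first row: 0.0109² / (16 × 0.09 × 0.958) = 0.000086; λ = 0.000086 × 10,240 = 0.88; power 0.155.

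**4. What the table shows.** The answer depends almost entirely on which effect on nature play is assumed, and the document supplies none. At 10% prevalence with the same absolute gain, f² (0.0055) exceeds the pilot's. With the same relative gain, it is about 3% of the pilot's (0.000086 / 0.00308).

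**The case against.** The article does not say outright that 0.997 is power for nature play. It describes the figure as power for the pilot's effect and states the change of outcome openly. That is fair, but the same calculation is the only basis given for 10 centers, so a reader will take it as the trial's power. The remark that the approach mirrors the pilot concerns how play proportions are compared; it gives no reason to expect the same effect size.

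A reader might infer that the trial is underpowered for nature play. The document does not support that. The low figures in the table need an equal relative gain, which is itself an assumption. Table 2 describes a program that adds plants and natural materials and teaches Land as Teacher, so a larger effect on nature play than on play in general is plausible. Correcting the outcome alone could move power either way.

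A reader might also infer that the pilot effect was picked because it was significant and is therefore inflated. The article calls it statistically significant but does not say that this was why it was chosen; it may simply be the effect on the pilot's main outcome.

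Finally, Results says data collection finished in March 2025, so no recalculation can change the sample, and confidence intervals will show the precision reached. This limits the consequence but does not make the printed justification apply to the primary outcome.

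**Conclusion.** The point holds as a mismatch between the power input and the primary outcome. The 0.997 reproduces, but it answers whether the trial could detect the pilot's effect on play versus nonplay. No power is stated for nature play, and the direction of the error cannot be told from the document.

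The illustrative range, 0.155 to about 1.0 at N=10,240 and 0.21 to about 1.0 at N=15,360, rests on assumed prevalences (80% for play, 10% or 20% for nature play), an assumed alpha of 0.05, one tested predictor, a balanced two-by-two layout and independent clips. It shows how undetermined the figure is and does not estimate the trial's power.

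**What to change.** State in Data Analysis that 0.997 applies only to the pilot's play-versus-nonplay effect and is not power for the primary outcome.

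Primary Outcomes says the TOPO was still used for coding, so pilot bio-play codes may exist. Where they allow it, replace the figure with the minimum detectable difference in nature-play proportion for the plan's own contrast (time 1 v time 2 in group 1, time 2 v time 3 in group 2). Base it on a stated base rate, a stated worthwhile difference in percentage points and a center-level ICC. Where a value must be assumed, show a range. A video-level ICC should not be expected from a pilot that was coded in situ at center level.

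The cost is one recalculation or one restated sentence. The sample stays as it is; what is given up is the claim of over 99% power for the primary question.

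### The coefficient named as key, an intervention-by-group interaction, does not match the before/after windows that define the program effect, so the 0.997 power is not shown to apply to that effect

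*Protocol article*

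**What the plan says.** All of this stands in the Data Analysis section of the protocol article unless noted.

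- **Effect behind the power figure:** the short-term impact seen in the pilot, taken over "time 1 vs time 2 for group 1 and time 2 vs time 3 for group 2".
- **Coefficient:** "The key coefficient of interest is the intervention by group interaction term".
- **Other model terms:** "5 control variables (ie, intervention, group, weather conditions, temperature, and child gender". Intervention and group thus enter as separate main effects, counted among the controls.
- **Size:** an R-squared "increase of 0.00295 (ie, variance explained by the special effect), equaling to an effect size of 0.00308", with the control terms described as those "which altogether correspond with a residual variance of 0.958".
- **Claim:** "This supports a power calculation of over 99% (0.997) to detect the program effect that we observed in the PRO-ECO 1.0 study".
- **Data:** "512 fifteen-second video clips at each center for each time point, for a total of 5120 video clips per time point (total N=15,360".
- **Planned comparison:** "we intend to evaluate the change in nature play behavior between pre- and postprogram". The article adds that this follows the pilot's analysis.

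The Randomization section says that group 1 started the program right after baseline, and that group 2, the waitlist control, started after time 2. Data were collected in fall and spring. Later in Data Analysis, mixed models are promised for comparisons between groups and within groups, without naming another key coefficient.

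**The concern.** In a model with a before/after term, a group term and their product, the product measures how much the before/after change differs between the groups. It measures a program effect only when one group is untreated during the interval compared. Over the stated windows neither group is: group 1 takes up the program between times 1 and 2, and group 2 between times 2 and 3. An effect common to both groups drops out of the product and sits in the intervention term, which the article lists as a control.

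At stake is what the power statement describes and which coefficient will be read as the result. On this coding the named term can be null when the program works. It can also be non-zero when the program does nothing but the two windows differ in period change. The comparison that randomization protects, time 1 to time 2 while group 2 is still untreated, is not identified as key.

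**Working it through.** **1. The article's own figure.** Effect size = R-squared increase / residual variance = 0.00295 / 0.958 = 0.00308, as stated. Power was recomputed from the noncentral F test for an R-squared increase with six predictors. Alpha is not stated, so 0.05 is assumed. Clips are treated as independent, as in a fixed regression calculation.

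- One tested term: 0.978 at 5,120 clips, 0.9999 at 10,240 and 1.000 at 15,360.
- Five tested terms: 0.997 at 10,240 clips, an exact match.

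The stated 0.997 is therefore reproducible. The match at 10,240 (two time points, 2 × 5,120) does not reveal the coding: each group's own window and a time 1 to time 2 analysis both use two time points per center.

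**2. What the interaction estimates over the stated windows.** Let E1 and E2 be the program effects in groups 1 and 2, and let p2 and p3 be the period levels at times 2 and 3 relative to time 1.

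- Group 1, time 1 to time 2: change = E1 + p2.
- Group 2, time 2 to time 3: change = E2 + p3 − p2.
- Interaction (group 1 minus group 2) = (E1 − E2) + (2 × p2 − p3).

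If E1 = E2, the program effect cancels. The interaction is exactly 0 only if the period changes also match, that is p2 = p3 − p2.

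**3. What a time 1 to time 2 comparison estimates.** Group 1 changes by E1 + p2 and group 2, still untreated, by p2. The difference is E1, the program effect, whatever the period change.

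**4. Numerical check.** The regression was solved on expected cell means. The effects and the shift at time 2 are assumptions for illustration, on the proportion scale. Time 3 is set at the time 1 level (p3 = 0), and weather and temperature are left out.

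| Effect, group 1 / group 2 | Shift at time 2 | Interaction, own windows | Interaction, all three time points, before/after coding | Group-by-time, times 1 and 2 |
|---|---|---|---|---|
| 0.10 / 0.10 | 0 | 0.00 | 0.00 | 0.10 |
| 0.10 / 0.05 | 0 | 0.05 | 0.05 | 0.10 |
| 0.10 / 0.10 | +0.05 | 0.10 | 0.05 | 0.10 |
| 0.10 / 0.10 | −0.05 | −0.10 | −0.05 | 0.10 |
| 0 / 0 | +0.05 | 0.10 | 0.05 | 0.00 |

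In the first row the intervention term carries the 0.10. The own-window value of 0.10 in the third row agrees with the program effect by coincidence: the last row gives the same 0.10 with no program effect. Where the true interaction is 0, its rejection rate is alpha, here 5%.

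**The case against.** **The coding is inferred.** The two windows formally describe the effect found in the pilot. The interaction comes in the next sentence, and 'intervention' is never defined. If it codes calendar period, time 2 versus time 1 in both groups, the same three terms form an ordinary difference-in-differences, and the interaction is the program effect, as the article calls it. How the pilot model was coded cannot be checked from this document. This stands as a limit on certainty, but it does not reconcile the text. The article bases this trial's power on those windows, describes the planned comparison as before versus after the program, and says that it follows the pilot. Period coding contradicts the window given for group 2, so on that reading the windows are what needs correcting.

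**The interaction appears only in the power paragraph.** The analysis text also promises between-group comparisons from mixed models, which could contain the randomized contrast. A reader might infer that the trial will certainly rest its conclusion on a coefficient blind to the program effect. The document does not go that far. It names one key coefficient, for the power, and no other.

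**Equal effects do not by themselves give zero.** A reader might infer that they do. Step 2 shows that the period changes must match as well.

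**Season may matter little.** A reader might infer a large seasonal bias, since group 1's window appears to run from fall to spring and group 2's from spring to fall. The article gives no seasonal difference in nature play. It says collection was timed for similar weather, and it lists weather and temperature as covariates, which would absorb part of any shift. The size of such a bias is therefore unknown. The covariates cannot, however, restore a common program effect to the interaction.

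**Details belong in a fuller plan.** The coding may be defined there. The point here is a mismatch between statements the article does make.

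**Conclusion.** The point holds as an inconsistency in the Data Analysis section. Under before/after coding, which the text favours, the named coefficient is the difference between the groups' program effects plus any difference in period change between their windows. It is 0 when both are equal across groups, and the 0.997 then does not describe power for the program effect: rejection falls to alpha. Under period coding the coefficient is right, but the stated windows are wrong. Either way the passage needs correcting.

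The cancellation is algebra and needs no assumed figures, only the before/after coding and the program timing given under Randomization. The 5% rests on an assumed alpha of 0.05. The percentage-point examples are illustrations, and no size of seasonal bias is claimed.

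**What to change.** Define 'intervention' and name one of these as the key coefficient:

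- **Group-by-time term, time 2 versus time 1**, from both randomized groups at those two time points. This is the difference in change while group 2 is untreated. Cost: it uses 10,240 of the 15,360 clips, and the time 3 results become separate estimates.
- **A single treated indicator** (group 1 at times 2 and 3, group 2 at time 3) in a mixed model with fixed effects for group and time point. This uses all three time points. Cost: it assumes one effect common to both groups that persists in group 1 at time 3.

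Then restate the power for the chosen term. The R-squared increase of 0.00295 cannot simply be carried over. It belongs to whatever the pilot's interaction measured, and to play versus nonplay rather than nature play. The article should say which pilot coefficient and coding it came from.

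No new data are needed. The change is to the analysis wording and the power statement. Since data collection ended in March 2025, the article should also state whether the coding was fixed before the outcomes were analyzed.
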